
### Study Objectives

In this study, we identified the causal impact of user-centered approaches to family planning counseling on women’s contraceptive preferences and decision making by means of a randomized controlled trial. In particular, we investigated two channels that have been hypothesized to play a role in contraceptive decision making: (1) a preference-based, targeted, user-centered approach to family planning counseling and (2) male involvement in family planning counseling. To this end, we tested the following 2 hypotheses:

A preference-driven, tailored, user-centered approach to counseling would allow women to express and realize their contraceptive preferences more effectively.The involvement of male partners in family planning counseling may allow women to express their contraceptive preferences and, in turn, translate their preferences into behavior more effectively.

The study population comprised married women aged 18-35 years living in Lilongwe, Malawi. As part of the trial, each woman in the study was randomly assigned to 1 of the 3 treatment arms or a control arm. A woman assigned to one of the intervention arms received one tailored, user-centered counseling session, followed by a package of family planning services that was designed to reduce the key barriers to accessing family planning in urban Malawi. The primary objective of this study is to evaluate the impact of user-centered counseling on a woman’s contraceptive use, intention to change stated ideal methods, switching of the current method, and realization of the stated ideal method. Primary outcomes include changes to women’s contraceptive method preferences (both stated and realized) over time and changes to women’s contraceptive concordance (whether a woman’s stated choice of contraceptive method, her ideal method, is the method that she is, in fact, using). Secondary outcomes include changes to male partners’ fertility and family planning preferences, women’s sexual and marital well-being, and changes in women’s decision-making in the household.

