### Randomization

Following the baseline survey, women who consented to participate were randomized into 1 of the following 4 experimental arms:

A control group (T0), in which a woman received a private counseling session on the full range of 13 contraceptive methods following a standard counseling process (n=100).An intervention group (T1), in which a woman was encouraged (but not compelled) to invite her husband to a joint counseling session. A woman (and her husband if she chose to invite him) then received a private counseling session on a full range of 13 contraceptive methods (n=200).An intervention group (T2), in which a woman received a private counseling session on 5 targeted contraceptive methods based on her baseline preferences for family planning (n=200).An intervention group (T3), in which a woman was encouraged to invite her husband to a joint counseling session. A woman (and her husband if she chose to invite him) was then counseled on 5 targeted contraceptive methods based on her baseline preferences for family planning (n=200).

Upon the completion of baseline data collection, women were randomized to 1 of the 3 intervention arms or the control arm, such that the intervention assignment was balanced along the following baseline characteristics: the use of family planning, most preferred method attributes, and age. As part of the balancing process, strata by each combination of characteristic values were created, and observations were assigned to their respective strata. Observations within each stratum were then individually randomized to each of the 4 groups by the principal investigator (PI) in a 2:2:2:1 allocation using computer-generated randomization using STATA, version 14 (StataCorp LLC). Following individual randomization, the Innovations for Poverty Action (IPA) Malawi intervention team implemented the intervention in the participants randomized into the intervention arms. Although the implementation team was not involved in the actual randomization process, counselors, who were responsible for administering the correct counseling and follow-up procedures to each respondent, were not blinded to respondent assignments to each of the intervention arms.

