### Primary Outcomes

Key primary outcome variables include the following:

Attitude or knowledge of family planning, including knowledge of family planning and perceptions toward contraception (eg, intentions to use)Contraceptive use, including changes in contraceptive use, changes in method mix, and adherence to methods (compliance, switching, and discontinuation)Contraceptive preferences, including the ideal contraceptive method and the most valued contraceptive method attributePregnancy and fertility outcomes, including pregnancy status, parity, delivery in a facility, months since last birth, wantedness of last birth, and intentions to become pregnant in the futureUse of local health facilities, including the frequency of visits to local clinics and frequency of receipt of family planning counseling servicesHusband’s preferences, including the approval of family planning and fertility preferencesWomen’s autonomy, empowerment, and decision making

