### Analysis Plan

The analysis of quantitative study data will be conducted using STATA and R (R Foundation), where appropriate. Descriptive analysis will be performed for all variables, and unadjusted comparisons between experimental arms will be conducted. Descriptive statistics, including frequencies, means, and SDs, will also be performed. Chi-square tests and one-tailed *t* tests will be used to examine associations in the data. A probability value of less than .05 will be considered statistically significant for all the statistical tests that are conducted. Continuous variables will be tested for normality, and nonnormal values will be categorized or appropriately transformed. Given our hypotheses regarding the impact of our intervention on our key outcomes, one-sided hypothesis tests will be conducted for all our main analyses.

Our main econometric specifications will (1) estimate the intent-to-treat (ITT) effects of our family planning intervention on fertility intentions and preferences, contraceptive intentions and preferences, intention to switch methods, and other outcomes related to contraceptive behaviors by directly regressing our outcomes of interest on a binary variable indicating receipt of the intervention and (2) estimate the effect of interventions on downstream behavioral outcomes (such as women’s uptake of contraceptive options and the concordance between their revealed preference and their stated preference) using a 2-stage least squares model, in which the intermediate counseling variable will be instrumented by the treatment. The main econometric specification for estimating the ITT effect of our family planning intervention is defined as follows:

*Y_it_* = *β_0_* + *β_1_T_it_* + *X_it_ζ* + *Y_i0_* + *η_i_* + *ε_it_*

where *Y_it_* is the outcome variable of interest for woman 𝑖 in time period 𝑡=0, 1, 2 for baseline (time period 0) and follow-up (time periods 1 and 2), respectively; *T_it_* is an indicator of assignment to 1 of the 3 treatment arms; *X_it_* is a vector of individual-level covariates that are controlled for in the analysis; η_i_ is the individual-specific fixed effect; *Y_i0_* is the baseline level of the outcome; and *ε_it_* is the error term. Here, the outcome variables of interest include immediate, intermediate, and long-term outcomes described in the previous sections.

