## Discussion

### Principal Findings

The primary objective of this study is to investigate the extent to which user-centered approaches to counseling, by exploiting choice architectural elements around family planning and promoting male involvement, can affect a woman’s immediate stated preferences and realized preferences in a context where her preferences may be sensitive to a range of behavioral biases. Our main outcomes of interest include women’s stated preferred method of contraception, intention to switch to other contraception methods, uptake of their ideal contraceptive method, and realization of their ideal contraceptive preferences. In addition, by observing whether women will seek family planning following their counseling visit, we will examine the short-run stability of their stated preferences and the extent to which these stated preferences are subsequently realized in the face of barriers to use. Data examining the realization of women’s eventual contraceptive preferences (eg, contraceptive uptake, eventual method choice) were collected during clinic visits and at (phone or home) follow-ups across the four arms.

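### The blanket one-sided rule is applied to contraceptive-preference outcomes that have no hypothesised direction, some of them unordered categories

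*Protocol article*

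**What the plan says.** The protocol article words the preference outcome in three ways.

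- **Study Objectives** frames it as change: "Primary outcomes include changes to women’s contraceptive method preferences (both stated and realized) over time", together with concordance between the ideal method and the method in use. The objective itself covers contraceptive use, "intention to change stated ideal methods, switching of the current method, and realization of the stated ideal method".
- **Primary Outcomes** lists contraceptive preferences as the categories themselves, "including the ideal contraceptive method and the most valued contraceptive method" attribute.
- **Discussion, Principal Findings** again lists the method itself: "stated preferred method of contraception, intention to switch to other contraception methods, uptake of their ideal contraceptive method".

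The **Analysis Plan** names contraceptive intentions and preferences among the outcomes of the intent-to-treat analysis. It estimates effects by "directly regressing our outcomes of interest on a binary variable indicating receipt of the intervention". It sets .05 as the threshold for every test and adds that "one-sided hypothesis tests will be conducted for all our main analyses", with no exception. Chi-square tests are mentioned for examining associations, separately from the main econometric specification.

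**The concern.** A one-sided test needs a stated direction. Contraceptive uptake and intention to switch have one: the power section assumes an increase in each. Which method a woman calls ideal, or which attribute she values most, does not. The methods are up to 13 unordered categories, and no section says which of them counts as the hypothesised side.

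Reading the outcome as change in the stated method makes it binary but does not settle the direction. Tailored counseling might move women to a new ideal method or confirm the one they already had, and the background section mentions reinforcement. The article also describes opposing effects of the husband's involvement.

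At stake is whether a listed primary outcome has a test with a defined hypothesis and a controlled error rate. Follow-up data collection has ended and analysis is described as ongoing, so a side chosen now could be chosen with the data in view.

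**Working it through.** **1. Is a direction stated?**

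| Outcome | Scale | Direction in the article |
|---|---|---|
| Contraceptive uptake | binary | increase (50% to 60% in the power section) |
| Intention to switch | binary | increase (20% to 30%) |
| Realization of, or concordance with, the ideal method | binary | improvement (the two study hypotheses) |
| Stated ideal method | unordered, up to 13 methods | none |
| Most valued attribute | unordered | none |
| Change in stated ideal method | can be coded 0/1 | either (below) |

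For change, two sections matter. Choice Architecture in Family Planning says that information tailored to valued attributes may reinforce a woman's preferences, which points to less change. Intention to Switch Methods: Partner Invitation Interventions says male involvement may encourage women to change their preferences or discourage them from changing their stated ones. It then commits to an increase, but only for intention to switch.

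**2. Reproduce the plan's own power figures.** Inputs: 300 versus 400 women, α = .05. Normal approximation with pooled variance under the null, where p̄ = (300p₁ + 400p₂)/700:

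SE₀ = √[p̄(1 − p̄)(1/300 + 1/400)], SE₁ = √[p₁(1 − p₁)/300 + p₂(1 − p₂)/400], power = Φ[(d − z·SE₀)/SE₁].

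- 50% v 60%: SE₀ = 0.03794, SE₁ = 0.03786. Two-sided: Φ[(0.10 − 1.960 × 0.03794)/0.03786] = Φ(0.677) = 0.751 (stated 75%). One-sided: Φ[(0.10 − 1.645 × 0.03794)/0.03786] = Φ(0.993) = 0.840 (stated 85%).
- 20% v 30%: SE₀ = 0.03338, SE₁ = 0.03253. Two-sided 0.856 (stated 86%); one-sided 0.917 (stated 92%).

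These figures reproduce within about one percentage point. All concern binary outcomes with a stated direction; none covers the stated method.

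**3. A one-sided test when the effect runs the other way.** The article gives no rate of change in stated ideal method, so the two planning rates are borrowed as an assumed range, with a 10-point fall and an upward test (d = −0.10).

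- 50% v 40%: Φ[(−0.10 − 1.645 × 0.03794)/0.03786] = Φ(−4.29), below 0.0001. Two-sided: Φ(0.677) = 0.751.
- 20% v 10%: SE₀ = 0.02673, SE₁ = 0.02754. Upward test: Φ(−5.23), below 0.0001. Two-sided: Φ[(0.10 − 1.960 × 0.02673)/0.02754] = Φ(1.73) = 0.958.

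**4. If the side is picked after looking.** Under the null the statistic exceeds +1.645 with probability .05 and falls below −1.645 with probability .05. Choosing the favourable side gives .05 + .05 = .10.

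**5. Unordered categories.** A joint comparison across several categories has no greater-than alternative, so the one-sided rule cannot be applied to it.

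**The case against.** The strongest reply is that Study Objectives already frames the outcome as change and concordance. Both can be coded 0/1, and the linear model then gives a valid risk difference. The exact coding of a survey item is commonly left to an analysis plan, and the article does name chi-square tests, which suit arm-by-method tables. The powered outcomes are binary with a stated direction.

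Most of this stands. A reader might infer that the plan regresses a numeric method code, so that the coefficient would depend on how the methods are numbered. A 10-point move between two of 13 methods would then give anything from −0.10 × 12 = −1.2 to +1.2. The documents do not support that reading: no section makes a method code the dependent variable, and the flip-chart orders in Table 2 are counseling materials, not outcome codes. Nor is the stated method clearly the leading outcome. It comes first only in the Discussion; Primary Outcomes begins with attitude or knowledge, and the objective begins with contraceptive use.

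The reply does not reach the one-sided rule. That rule is stated, covers all main analyses, and makes no exception for outcomes without a direction. Coding the outcome as changed or not changed does not supply a direction. Chi-square is offered for associations, outside the main specification.

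**Conclusion.** The point holds as a defect in the stated testing rule, together with inconsistent wording of the preference outcome across three sections. For the stated method and the most valued attribute, the one-sided test is undefined. For change in the stated method, it has almost no chance of detecting a 10-point effect on the untested side (below 0.0001 in both assumed scenarios), or it runs at .10 if the side is chosen after seeing the data. The first figure rests on borrowed rates, since the article gives none for change; the second is exact for a symmetric test statistic.

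The conclusion does not extend to uptake, intention to switch or the sample size, nor does it show that the linear model is invalid for a 0/1 preference outcome. It also does not establish that any grouping of methods was or will be chosen with sight of the results.

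**What to change.** 1. Use the Study Objectives form throughout: a binary outcome, stated ideal method differs from the ideal stated at baseline. Keep the linear model and test two-sided at .05. The baseline-outcome term is zero for every woman under this definition and drops out.
2. Compare the distributions of stated methods and of valued attributes across the two randomised factors with an order-free joint test, such as chi-square or a multinomial logit with a joint Wald test. Fix any grouping of rare methods blind to arm.
3. In the Analysis Plan, exempt these non-directional outcomes from the one-sided rule.

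The change is a few lines of text and standard software. The cost is power. By the article's own figures, moving from one-sided to two-sided takes 85% to 75% for prevalence and 92% to 86% for switching; a similar loss would apply to change if the direction had been guessed correctly. For the joint test, the article gives no method shares. Assuming shares of 30, 15, 12, 10, 8, 6, 5, 4, 3, 3, 2, 1 and 1% and 300 versus 400 women, a 12-degree-of-freedom chi-square has about 20%, 74% and 99% power for shifts of 5, 10 and 15 points from the commonest to the second commonest method. Pooling the six methods below 5% into one group (7 degrees of freedom) raises the 10-point figure to about 83%.

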### Study Limitations

Our study has several limitations. Although the study is powered to independently test the effects of 2 user-centered counseling procedures on women’s stated and realized preferences, the sample size of this study may be too small to allow for the examination of interaction effects across treatment arms. As an exploratory exercise, we will examine these effects and present them as supplementary findings. Moreover, although our study can infer the manner in which women realize their preferences in response to counseling, it is not as straightforward to be able to disentangle a woman’s true individual preferences for family planning from her stated preferences in the presence of her partner, who is likely to influence her eventually realized choice (or lack of choice) of method. To this end, additional research is warranted to better understand how women’s true preferences are expressed and can be documented, even in cases where their partner is present. Similarly, it would be equally necessary to further explore the trade-off that women face between (1) making independent decisions to reflect their individual preferences and (2) incorporating their husband’s/family’s preferences to make jointly/socially better-off, but not necessarily individually better-off, decisions.

### Conclusions

Our study findings seek to inform women and communities of the local family planning environment. In addition, our findings will inform both clients and service providers of the role of user-centered, tailored family planning counseling in improving concordance between a woman’s preferences and her contraceptive use, which in turn would help her realize her family planning goals. The results may also help the MOH and other service providers to develop family planning programs that internalize the preferences of women and their partners for contraceptive methods, thereby achieving the goal of improving reproductive health outcomes in Malawi. More generally, our findings may also demonstrate to policy makers that the benefits of tailoring family planning services to women’s preferences are likely to extend beyond the health domain by improving empowerment outcomes. Such findings can be used to develop policies, programs, and interventions that aim to improve the health and well-being of women, couples, and households.

## Appendix

Multimedia Appendix 1 Survey instruments, recruitment scripts, and consent forms.

Multimedia Appendix 2 Family planning flip charts.

## Abbreviations

BCS: Balanced Counseling Strategy
BLM: Banja La Mtsogolo
BU: Boston University
DHS: Demographics and Health Survey
HIPAA: Health Insurance Portability and Accountability Act
IPA: Innovations for Poverty Action
IRB: institutional review board
ITT: intent-to-treat
MDHS: Malawi Demographics and Health Survey
MOH: Ministry of Health
NHSRC: National Health Sciences Research Committee
PI: principal investigator
PSI: Population Services International
RHD: Reproductive Health Directorate
